#### Exclusion criteria

The exclusion criterion for all participants is:

No access to the internet (in order to use the digital platform) and impossible to arrange this (eg, at one’s medical/community centre).

### Intervention

The intervention around which this evaluation study revolves is a digital platform aimed at HSCPs and LLP migrants and refugees (as well as their (informal) caregivers). The platform was developed following the STAR model^41^ for eHealth interventions, which provided a rigorous participatory engagement model to optimise the involvement of these end users. The model consists of five phases (‘listen’, ‘plan’, ‘do’, ‘study’ and ‘act’). First (‘listen’), a mixed-method approach was applied to map resources as well as the most severe barriers, salient needs and recommended communication strategies for both HSCPs and LLP migrants and refugees.^14 39 40^ Second (‘plan’), audiovisual communication strategies in the form of animated videos were developed in Vyond for LLP migrants and refugees^44^ and for HSCPs (*publication in progress*). Third (‘do’), building on these insights from previous parts of the project, the platform was developed. The current study focuses on the fourth and fifth phases (‘study’ and ‘act’) of the STAR model^41^ in which the intervention will be implemented and evaluated in practice.

The platform (see: www.mentalhealth4all.eu (pending positive results, the platform will only be available for participants with a personal code for the duration of the current study)) consists of different informative elements, related to the different dimensions of access, including:

Availability: a map of Europe that shows the presence of several organisations that provide (culturally sensitive) mental healthcare.Approachability: one set of eight videos aimed at LLP migrants and refugees with information on, for example, available services, mental health conditions and the healthcare system.^44^Acceptability: one set of 10 videos aimed at HSCPs, for example, about working with interpreters, communication strategies and recognising/addressing mental health issues in migrants and refugees (*publication in progress*).Appropriateness: a resource repository/information portal where users can select/search for the information they need from an exhaustive set of multilingual materials such as documents or videos about mental health or language services.^40^

The platform can be used on different devices, including computers/laptops, tablets and smartphones. For the current evaluation study, the platform will be available in fifteen languages: Dutch, English, French, German, Italian, Lithuanian, Polish, Slovak, Spanish (ie, the dominant languages of the participating countries), Arabic, Chinese, Persian, Russian, Turkish and Ukrainian (ie, languages representing large migrant language groups in Europe).

For the HSCPs, we have developed an accompanying, standardised training to teach them how to work with the platform and how to integrate it into their clinical practice. The training consists of two parts:

A general online webinar for HSCPs on how they can use the platform in practice—which is uploaded on the platform and available in the dominant languages of the nine participating countries.A personalised, structured training session (either individual or in a group, and online or in-person) in which more detailed discussions will be held with a trainer on how to implement the (content of the) platform in the HSCPs’ daily practice, for which a standard training outline with a model presentation was developed to promote consistency across trainers/countries.

### Patient and public involvement

LLP migrants and their representatives have been involved in the entire MentalHealth4All project, including the original project proposal and (the preparations for) the current study. For example, the Foundation for the Health of Immigrants in the Netherlands has been involved as a consortium partner since the start of the project. Moreover, different platform components were cocreated with and/or pilot tested by LLP migrants as well as providers. Migrant representatives will also be involved in spreading the word about the project/study among other LLP migrants and refugees.

### Procedures

This study will be carried out in nine countries represented in the MentalHealth4All consortium: Belgium, Germany, Italy, Lithuania, the Netherlands, Poland, Slovakia, Spain and the UK. In all nine countries, we will use convenience sampling by approaching HSCPs through our existing networks and by reaching out to relevant professional organisations (eg, psychologists, social workers). Each HSCP will be asked to approach migrants and refugees who are, for example, on a waiting list or have only recently started treatment to participate in the study. Additionally, migrants and refugees will be recruited via key figures in communities that cover the target audience of this study, for example, social workers in neighbourhood facilities, cultural/religious leaders, general practitioners/family doctors and other prominent figures in social contexts. Besides, messages across refugee/migrant social media pages, migrant/refugee/professional organisations and the project’s social media channels will call for participants who meet the relevant criteria. Migrants and refugees who are interested can voluntarily reach out to the research team. We will also ask participants (migrants/refugees and HSCPs) if they may know others who would want to participate in this study (ie, ‘snowballing’). Before participation, all migrants/refugees and HSCPs will receive an information factsheet about the study and an informed consent form. We will use easy-to-understand information materials in multiple languages, that is, in the participants’ mother tongue or a possible second language. Multilingual research assistants will be available to help (verbally) discuss the information in participants’ mother tongue and answer possible questions.

After agreeing to participate, participants will receive the link to the questionnaires (see online supplemental appendix 1) and a personalised log-in code (for both the questionnaires and the platform). Participants will then be asked to go through three different steps, as illustrated in figure 1. First, participants will be asked to fill out the pretest questionnaire to establish a baseline, which starts by asking informed consent (T0). Second, they will be asked to use the multilingual digital platform/intervention (T1; ie, for HSCP participants, this also includes participation in personalised training). Third, participants will be asked to fill out the post-test questionnaire to evaluate the platform’s effects on the four dimensions of access to mental healthcare immediately after having used the platform (T2). Fourth, after about 6–8 weeks after T1, HSCPs will participate in a brief phone or online interview to answer some final questions on their usage of/experiences with the digital platform and its effects on access to mental healthcare (T3). The digital platform and the questionnaires will be available online in multiple languages in order to match participants’ mother tongue or a possible second language. If a participant prefers, the surveys could be administered on paper or verbally, for instance, by a (multilingual) research assistant or with the possible help of an interpreter.

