**Methods and analysis:**

We will conduct a pretest–post-test cross-national survey study to evaluate the platform’s effect evaluation (primary objective) and process evaluation (secondary objective). The primary outcomes (measured at T0, T2 and T3) are four dimensions of access to mental healthcare services: availability, approachability, acceptability and appropriateness of mental healthcare. Secondary outcomes (measured at T2) are: actual usage of the platform (ie, tracking data), perceived ease of use, usefulness of content, comprehensibility of information, attractiveness of content and emotional support. Participants will be recruited from nine European countries: Belgium, Germany, Italy, Lithuania, the Netherlands, Poland, Slovakia, Spain and the UK. Using convenience sampling through professional networks/organisations and key figures, we aim to include at least 52 HSCPs (ie, 6–10 per country) and 260 LLP migrants (ie, 30–35 per country). After completing a pretest questionnaire (T0), participants will be requested to use the platform, and HSCPs will participate in an additional personalised training (T1). Next, participants will fill out a post-test questionnaire (T2) and will be requested to participate in a second post-test questionnaire (T3, about 6–8 weeks after T2) to answer additional questions on their experiences through a brief phone interview (T3 is optional for migrants/refugees).

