## Methods and analysis

### Study design

To answer the research questions, a pretest–post-test cross-national study will be conducted to evaluate the MentalHealth4All digital platform in nine European countries (ie, Belgium, Germany, Italy, Lithuania, the Netherlands, Poland, Slovakia, Spain or the UK). These countries were selected as consortium partners to ensure broad geopolitical representation across northern, eastern, southern and western Europe. Due to the nature of the study design and intervention, either randomising or blinding participants is not possible. We will apply an intention-to-treat approach,^42 43^ that is, including participants regardless of how long they have used the digital platform. This approach aligns well with actual practice where, for instance, some people may search for specific information and therefore briefly use a specific part of the platform, while others may go through the entire platform to explore what possibilities there are. For each country, the ethical review board of the participating university/hospital has assessed and approved the protocol.

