#### Primary outcome measurements

In line with RQ1, the main study parameter is access to mental healthcare services, measured by means of four dimensions, that is, availability, approachability, acceptability and appropriateness.^37 38^ These four dimensions are the main endpoints for this study. Based on other existing questionnaires, we selected and/or developed our own questions to assess these dimensions. In particular, we used existing scales for mental health literacy,^45^,^47^ and the Canadian Community Health Survey on accessibility, acceptability and availability^48^ as inspiration for these endpoints. Additionally, we supplemented the dimensions with statements that were considered of particular relevance in the current context (ie, migrants/refugees and mental health) based on the extensive expertise of the project team. These primary outcome measurements will be assessed at T0 (pre test), T2 (first post test) and T3 (second post test).

*Availability of care*: the presence and capacity of facilities will be assessed with five items on a five-point Likert scale (1=strongly disagree, 5=strongly agree).*Approachability of care*: this dimension entails access to information on (patient) rights, services available and costs of services and will be assessed with seven items on a five-point Likert scale (1=strongly disagree, 5=strongly agree).*Acceptability of care*: this dimension assesses providers’ cultural competence and will be assessed with four items on a five-point Likert scale (1=strongly disagree, 5=strongly agree).*Appropriateness of care*: this dimension indicates how well the services provided match the needs of the refugee/migrant populations and will be assessed with six items on a five-point Likert scale (1=strongly disagree, 5=strongly agree).

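### For migrants recruited near entry into care, the T0–T3 change in perceived access mixes the care pathway with the platform, and the article lists no measure of care status to tell them apart

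*Protocol article*

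**What the plan says.** All references are to the protocol article.

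- **Recruitment (Procedures).** Providers are asked to approach migrants and refugees who are, for instance, "on a waiting list or have only recently started treatment to participate in the study". There are other routes: "Additionally, migrants and refugees will be recruited via key figures in communities that cover the target audience of this study". Social media, organisations and snowballing are also used. None of these routes requires a care-pathway status.
- **Design (Study design).** The study is pretest–post-test without a comparison group. The reason given is: "Due to the nature of the study design and intervention, either randomising or blinding participants is not possible".
- **Endpoints (Primary outcome measurements).** Availability, approachability, acceptability and appropriateness of care are all primary, at T0, T2 and T3. Their content includes capacity of facilities, cultural competence of providers and fit of services to needs.
- **Timing.** T2 follows platform use immediately (Procedures). The abstract places "T3, about 6–8 weeks after T2" and makes it optional for migrants. Procedures instead has "after about 6–8 weeks after T1, HSCPs will participate in a brief phone or online interview" and does not mention migrants at that step.
- **Analysis (Statistical analysis).** One-sided t-tests and repeated-measures ANOVAs compare the pretest with the post-tests, separately for migrants and providers. Neither post-test is singled out as the one that carries the effect statement.
- **Interpretation (Introduction).** The primary objective and the first research question read the change as the effect of the platform.
- **Controls and limitations.** The T0 measures for migrants cover sociodemographics, reason for leaving and length of residence, mental health status, health and eHealth literacy, and language proficiency. Waiting-list or treatment status is not listed. The strengths and limitations box mentions neither the missing comparator nor entry into care during the study.

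**The concern.** Any uncontrolled pre–post study is open to changes that occur anyway. The problem here is more specific, because one recruitment route points to people whose access is likely to change during follow-up. Someone waiting at T0 may be in care by T3, and someone who has just started may by then have settled in. Either experience bears directly on how that person rates availability, acceptability and appropriateness.

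A rise from T0 to T3 among migrants could then be read as a sustained platform effect when part of it reflects progress along the care pathway. That reading matters, because the article ties public release of the platform to positive results. Unless care status is recorded, the two explanations cannot be examined side by side.

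**Working it through.** **The plan's own figure.** The Sample size calculation section gives n = 52 for a within-subject repeated-measures ANOVA with 2 groups, 2 measurements, alpha 0.05 and power 0.80. With noncentrality λ = f²·N·m/(1−ρ), f = 0.2, m = 2 and ρ = 0.5, N = 52 gives λ = 0.04 × 52 × 2 / 0.5 = 8.32 and power 0.8075, while N = 51 gives 0.7996. So 52 is reproduced with f = 0.2 and a correlation of 0.5, which the article does not state. I use the same correlation below.

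**Inputs for the illustration.**
- From the article: one-sided test, significance level 0.05, 260 migrants.
- Assumed: pre–post correlation 0.5, no platform effect, and a mean drift d in SD units caused by the care pathway. The article gives no value for any of these.
- Assumed: 130 migrants (half) complete the optional T3, as an alternative to all 260.

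**Uniform drift.** The standard error of the mean change in SD units is √(2(1−ρ)/n).
- n = 260: √(1/260) = 0.0620
- n = 130: √(1/130) = 0.0877

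The rejection probability is Φ(d/SE − 1.645). For d = 0.10:
- n = 260: Φ(1.612 − 1.645) = 0.487
- n = 130: Φ(1.140 − 1.645) = 0.307

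The noncentral t distribution gives almost the same values:

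| Mean drift (SD) | n = 260 | n = 130 |
|---|---|---|
| 0 | 0.05 | 0.05 |
| 0.05 | 0.20 | 0.14 |
| 0.10 | 0.485 | 0.305 |
| 0.20 | 0.94 | 0.73 |

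A mean drift of 0.10 SD arises if, say, a quarter of migrants shift by 0.4 SD (0.25 × 0.4) or half shift by 0.2 SD (0.5 × 0.2). A two-sided test at that drift rejects with probability 0.362 (n = 260) or 0.205 (n = 130), so the problem does not depend on the one-sided test.

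**Only a fraction shifts.** If a share p moves by 1 SD and the rest do not move, the mean drift is p, but the variance of the change also grows by p(1−p). For p = 0.15:
- variance = 1 + 0.15 × 0.85 = 1.1275, so SD = 1.062
- standardised drift = 0.15/1.062 = 0.141
- n = 260: Φ(0.141 × √260 − 1.645) = Φ(0.63) = 0.74
- n = 130: Φ(0.141 × √130 − 1.645) = Φ(−0.03) = 0.49

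**The case against.** Several points on the other side stand.

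- **Reach.** A reader might infer that migrants in general are recruited from waiting lists. The article does not say so: this is an example within one of several routes, and eligibility does not require a mental health problem. The affected share is unknown.
- **Timing.** T2 comes straight after platform use, and Procedures describes it as the measurement that evaluates the platform's effects. T3 is optional for migrants. The main exposure is therefore the T0–T3 comparison, and T0–T2 is much less affected.
- **Direction.** It is tempting to call the direction of the bias known. It is not: a person still waiting may rate availability lower, and a first consultation across a language barrier may lower acceptability. Upward is the more likely direction, no more than that.
- **Measurement.** Supplemental appendix 1, which holds the full questionnaires, is not shown and may already ask about care. The article supports only the statement that care status is not among the control measurements it lists.
- **Restricting to unchanged care status.** This looks like a clean effect analysis but is not. The platform is meant to promote access, so starting care may be one of its effects. Such a restriction conditions on a post-intervention variable.
- **Randomisation.** The article says of the platform that "the platform will only be available for participants with a personal code for the duration of the current study", and a reader might conclude that a randomised delayed start is feasible and that the statement on randomisation is wrong. The code shows only that individual log-in can be delayed. Providers trained on the platform also recruit migrants, and snowballing links participants, so contamination is a real risk. After a short delay both halves would have the platform well before T3, which leaves the T0–T3 drift uncontrolled.

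None of this removes the attribution problem. T3 is still listed as a primary timepoint without exception for migrants, and the change is still read as the platform's effect.

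**Conclusion.** The concern holds in a limited form. For the unknown share of migrants recruited while waiting for or just starting care, the T0–T3 change in perceived access cannot be attributed to the platform, and the listed control measurements give no means of describing the overlap. The likely direction favours the platform.

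The size cannot be derived from the article. The calculation shows only that a small drift is enough: at an assumed mean of 0.10 SD the false-positive rate is about 49% (n = 260) or 31% (n = 130). At 0.05 SD it is 20% or 14%. These figures rest on the assumed correlation, drift and T3 completion. T0–T2 also lacks a comparator, but it leaves far less room for this particular mechanism. The point is a worthwhile, inexpensive improvement and does not invalidate the design.

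**What to change.** 1. **Record care status.** Unless appendix 1 already does so, add a short item at T0 (none / on a waiting list / in treatment and since when), and at T2 and T3 an item on care started or changed since T0.
2. **Match the claim to the timepoint.** Base the platform-effect statement for migrants on T0–T2. Report their T0–T3 result as change over time and not as a platform effect. Show it descriptively by care status at T0 and by care started since, with a note that starting care may itself be an effect of the platform.
3. **State the limitation.** Name the missing comparator and concurrent entry into care among the study's limitations.
4. **Reconcile the T3 description.** The abstract and Procedures differ on whether T3 is timed from T2 or T1, and on whether migrants take part. The sections on primary outcomes and other measurements, which expect T3 data from migrants, should agree with whatever is settled.

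The cost is two or three extra questions and a more modest claim for migrants at T3. Sample size and recruitment do not change.

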**Ethics and dissemination:**

For all nine countries, the ethical review board of the participating university (hospital) has assessed and approved the protocol. If successful, the MentalHealth4All platform will be made publicly available to help improve access to mental healthcare services, as well as HSCPs’ cultural competencies in delivering such services, for any LLP migrants and refugees across Europe (and beyond). Findings will also be disseminated through peer-reviewed journals and conferences.

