Despite their great potential, evidence-based digital interventions to promote access to mental healthcare services for these target groups across Europe are still very scarce and often not properly evaluated in terms of their effectiveness.^35^ The MentalHealth4All project aims to fill these gaps by designing and evaluating a culture-sensitive multilingual digital platform to promote this access, which is defined as ‘the *opportunity* to use health services, reflecting an understanding that there is a set of circumstances that allows for the use of appropriate health services’.^36^ This evaluation study will primarily focus on four dimensions of access, namely: availability (ie, the presence and capacity of facilities), approachability (ie, access to information on (patient) rights, services available and costs of services), acceptability (ie, cultural competence by providers) and appropriateness (ie, how well the services provided match the needs of the refugee/migrant populations).^37 38^ Building on insights from previous parts of the project^14 39 40^ and following the Spiral Technology Action Research (STAR) Model,^41^ an evidence-based sustainable digital information and communication platform was cocreated with LLP migrants and refugees in order to promote their access to mental healthcare on these four dimensions.

This study protocol describes the final part of the MentalHealth4All project, which aims to prospectively evaluate the intervention in practice across nine European countries. The primary objective of this study is the effect evaluation, that is, to evaluate the effects of the digital platform on the main dimensions of perceived access to mental healthcare services.^37 38^ The secondary objective of this study is the process evaluation, that is, to evaluate the digital platform with regard to the process of implementing the platform in healthcare practice. Corresponding with these objectives, we will answer the following research questions:

*RQ1*. How does the digital platform affect participants’ (ie, migrants/refugees and HSCPs) perceptions of access to mental healthcare in terms of: (1) availability, (2) approachability, (3) acceptability and (4) appropriateness?

*RQ2*. How do participants (ie, migrants/refugees and HSCPs) use the digital platform in terms of the pages/videos they access and average duration of engagement?

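### For providers (HSCPs), the RQ1 before-after change is that of platform, webinar and trainer-led session together, but the objective, RQ1, the T2 sentence and the release statement credit the platform alone

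*Protocol article*

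**What the plan says.** **The question.** The Introduction gives the primary objective as "to evaluate the effects of the digital platform on the main dimensions of perceived access to mental healthcare services". RQ1 asks: "How does the digital platform affect participants’ (ie, migrants/refugees and HSCPs) perceptions of access to mental healthcare", on four dimensions.

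**What HSCPs receive.** The Intervention section describes a two-part training for HSCPs. One part is a webinar that sits on the platform. The other is a structured personalised session, individual or in a group, "in which more detailed discussions will be held with a trainer on how to implement the (content of the) platform". Procedures places this session in T1: "for HSCP participants, this also includes participation in personalised training". The abstract gives the same order: "participants will be requested to use the platform, and HSCPs will participate in an additional personalised training (T1"), followed by T2.

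**What is measured, and when.** Primary outcome measurements lists the access dimensions at T0, T2 and T3. Procedures says that at T2 participants will "fill out the post-test questionnaire to evaluate the platform’s effects on the four dimensions of access to mental healthcare immediately after having used the platform".

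**What follows from success.** The abstract's ethics and dissemination paragraph says that, if results are good, "the MentalHealth4All platform will be made publicly available to help improve access to mental healthcare services", and adds HSCPs' cultural competencies as a second benefit. It does not mention the personalised session.

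**How the Discussion puts it.** There the object of evaluation is the platform with additional training for HSCPs, which is wider than the exposure named in RQ1.

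**The concern.** In HSCPs, no access score is taken after platform use and before the live session, and no HSCP is planned to use the platform without it. A before-after difference in this group belongs to the whole package. RQ1, the primary objective and the T2 sentence nonetheless attribute it to the platform.

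Acceptability, one of the four primary dimensions, is defined as providers' cultural competence. A session with a trainer on using the content in daily practice could plausibly move that score. The release statement then names the platform as the thing that would improve those competencies. A good HSCP result could thus be quoted in support of a component whose own contribution was never observed. Migrants have no such session, so the same research question refers to a different intervention in each group.

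**Working it through.** **1. Sequence for HSCPs**

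| Step | What happens | Source |
|---|---|---|
| T0 | Access items, baseline | Procedures; Primary outcome measurements |
| T1 | Platform use and personalised session | Abstract; Intervention; Procedures |
| T2 | Access items | Procedures; Primary outcome measurements |
| T3 | Access items again | Procedures; Primary outcome measurements |

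The abstract times T3 from T2 and Procedures times it from T1. Under either reading T3 comes after the session. Read alone, the T2 sentence could suggest a measurement straight after platform use and before training. The numbered steps in Procedures and the order in the abstract rule that out.

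**2. What the HSCP contrast contains**

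Let P be the change due to the platform with its webinar, S the further change due to the live session (including any interaction with P), and B everything else that moves scores between T0 and T2, such as time, repeat testing and response bias. Then

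T2 − T0 = P + S + B.

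The design observes only the sum. There is no control group to estimate B and no untrained HSCP group or intermediate measurement to separate S. Even if B were zero, P could not be recovered from P + S. In migrants S is absent by design, so their contrast is P + B.

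**3. What the planned sample size addresses**

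Inputs from Sample size calculation: effect size 0.2, alpha 0.05, power 0.80, two measurements, n = 52. The correlation between measurements is not given; I assume ρ = 0.5. Reading 0.2 as Cohen's f:

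λ = f² × N × m / (1 − ρ) = 0.04 × 52 × 2 / 0.5 = 8.32.

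This gives power 0.807 with two groups and 0.808 with one, and 52 is the smallest N that reaches 0.80, so the stated figure is reproduced. The same λ corresponds to a standardised change of √(8.32 / 52) = 0.4. The 52 therefore powers a test of the total HSCP change.

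**4. Illustration of what that total can hide**

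Assume B = 0, a total standardised change of 0.4, and a two-sided 0.05 test with n = 52. The trial's test has about 81% power however the 0.4 divides between P and S. Had only the platform's share been present, power would have been:

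| Platform's share of 0.4 | Standardised change | Power at n = 52 |
|---|---|---|
| 100% | 0.4 | 81% |
| 75% | 0.3 | 56% |
| 50% | 0.2 | 29% |
| 25% | 0.1 | 11% |
| 0% | 0 | 5% |

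The document gives no evidence on which row applies, and the planned data cannot distinguish them.

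**5. Extent**

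All HSCPs: at least 52, or 9 × 6 = 54 to 9 × 10 = 90 from the per-country targets. All four primary dimensions: 5 + 7 + 4 + 6 = 22 items.

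**The case against.** The strongest reply is that nothing is concealed. The training is described under Intervention, Procedures defines T1 for HSCPs as including it, the strengths and limitations list gives its purpose, and the Discussion names it as part of what is evaluated. Testing a tool together with its onboarding is a legitimate pragmatic choice, and the session is about using the platform's content, so it is not an unrelated co-treatment. On this view RQ1 merely uses shorthand. That stands as far as it goes: the package is a sound thing to evaluate. It does not bring the objective, RQ1, the T2 sentence and the release statement into line with the package.

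A second reply is that, without a control group, the platform's effect is not firmly identified anyway. That is also true. The bundling is a further limit, confined to HSCPs, and would remain if time trends and testing effects were nil.

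Four stronger readings are tempting, and the document does not support them:

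- *Nothing learned from HSCPs concerns the platform.* Tracked usage (RQ2) and ratings of ease, usefulness, comprehensibility, attractiveness and emotional support (RQ3) do concern it, though as used by trained HSCPs.
- *The platform will be released without training.* The release statement does not mention the session, but nowhere is it said that it will be withheld. The webinar is on the platform and would go with it.
- *Migrant and HSCP results will be merged into one effect.* Statistical analysis treats the two groups separately.
- *One more questionnaire before the session would isolate the platform.* It would give P + B at best, and only if platform use came first. The text gives no order within T1, and Figure 1 is not available here.

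**Conclusion.** The point holds as a mismatch between the HSCP intervention delivered and the one credited. For HSCPs, RQ1 as planned can describe the change in perceived access after platform, webinar and personalised training together. It cannot say how much of that change is the platform's. This applies to every HSCP and to all four primary dimensions in that group. It does not apply to migrants, and RQ2 and RQ3 are not affected in this way.

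The conclusion rests on the stated order of T0, T1, T2 and T3 and on the absence of an HSCP group without the session. It does not depend on the sample size, the assumed correlation or the illustrative shares. The study remains usable. What should change is the wording of the HSCP half of the primary objective and of the claim that would follow from it.

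**What to change.** 1. For HSCPs, restate the primary objective, RQ1 and the T2 sentence in Procedures as the change in perceived access after platform plus webinar plus personalised training. The Discussion's description already points this way.
2. Limit the HSCP conclusion, and the release claim about HSCPs' cultural competencies, to that package. If the platform is offered without the session, say that this form was not evaluated in HSCPs on the access outcomes.

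The cost is wording and a narrower HSCP claim. No data collection or analysis changes.

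Optionally, HSCPs could complete the 22 access items once more just before the session. This adds a short questionnaire for about 52 to 90 people and one more repetition of the items. It also requires platform use to come before the session, which may alter the intervention as delivered. The result would be descriptive only and should not be reported as a platform-only effect.
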